### 3.4 Narrative of Study Procedures

Prior to initiating any study-related procedures, all participants must provide written informed consent in accordance with Research Ethics Board (REB) requirements and applicable regulations.

Individuals who express an interest in participating in the study will be contacted, by phone, by a designated member of the research team. During the telephone call, the individual will answer specific questions in order to assess their eligibility for the study. If the participant meets the pre-screening requirements, the individual will be invited to schedule a screening visit no more than 2 to 30 days prior to the anticipated baseline (Day 0) visit with a study coordinator. Subjects will be asked to come to the screening visit fasting (nothing to eat or drink except water for at least 12 hours prior to the visit) and avoid consuming alcohol for at least 24 hours prior to the visit.

#### 3.4.1 Visit 1 (-1 to -30 days prior to Day 0 – Screening Visit)

At this visit, the individual will meet with a study coordinator who will provide the individual with an informed consent form (ICF), which the individual will read and sign. Each participant will be given sufficient time to read the information carefully and ask the coordinator for more information. If necessary, the participant will also be given the option of taking the consent form home to review prior to making his/her decision to participate in the study.

**Contraception:** Women of childbearing potential (women who are not surgically sterile, or post-menopausal status) will be instructed to take the necessary precautions to avoid pregnancy for the duration of the study period. Women of childbearing potential must agree to one of the following acceptable contraceptive methods:

- Continuous use of oral or long acting injected contraceptive for at least 2 months prior to study entry , or
- Use of an intra-uterine device or implantable contraceptive, or
- Use of double barrier methods of birth control, or
- Abstinence from heterosexual intercourse

Women who are surgically sterile (or women with surgically sterile partners), and women who have achieved post-menopausal status (absence of menses for at least 12 months) will not be required to use contraceptive methods.

Once written informed consent is obtained from the participant, demographic and medical history data will be collected and a physical examination (excluding rectal / genital examination) will be performed. Biometrics (height and weight) and vital signs (seated resting blood pressure and heart rate) will be measured, and BMI calculated. Inclusion/exclusion criteria will be reviewed in order to confirm eligibility. If the participant does not meet the study requirements, the participant will be considered “screen failed”. Participants will be asked to complete a food frequency questionnaire to determine their omega-3 consumption habits. Changes in medical conditions and medications will be reviewed. Blood pressure, and weight will be measured and BMI calculated. A blood sample will be collected for analysis of CBC, glucose, AST, ALT, BUN, creatinine, eGFR, electrolytes (Na, K, Cl), and lipid profile (total cholesterol, LDL-C, HDL-C and triglycerides). Inclusion and exclusion will be reviewed in order to confirm eligibility. If the

participant does not meet the study requirements, the participant will be considered “screen failed”. Eligible subjects will be scheduled for visit 2 and reminded to avoid consuming alcohol for at least 24 hours prior to visit 2.

### **3.1.1 Visit 2 (Day 0) [Baseline; Randomization]**

Eligible subjects will return to the clinic for baseline assessments.

Participants who satisfy the study requirements will proceed with the following visit procedures:

- Urine pregnancy test (for women of childbearing potential only). If positive, individual will be deemed ineligible to participate, and will be considered “screen failed”.
- Collection of vital signs (seated resting blood pressure and heart rate)
- Measurement of weight and calculation of BMI
- Review changes in medication / medical conditions
- Review of inclusion / exclusion criteria
- Blood sample: Serum phospholipid fatty acids and red blood cell fatty acids
- Randomization to treatment
- Administration of IP and IP dispensed
- Daily treatment diary will be dispensed

Subjects will be randomized to one of the following treatment regimens:

- Ultimate Omega® (5 capsules once per day in the morning with food) for 168 days
- Meg-3™ (5 capsules once per day in the morning with food) for 168 days

Subjects will be given detailed instructions by site personnel about the dosing regimen. Subjects will be instructed to take the first dose of the study product in the clinic with a snack. Subjects will remain in the clinic after taking the treatment for 15 minutes for observation.

Paper diaries will be provided to subjects for recording study product use, change in concomitant therapies, and any side effects/changes in current conditions.

Subjects will be reminded not to change dietary habits and activity/training level during the study and to avoid consuming alcohol for at least 24 hours prior to the next study visit.

The next visit will be scheduled for Day 28. In the event that this is not possible due to subject scheduling issues, a visit window of  $\pm 2$  days may be applied. Subjects will be asked not to take their study product on the morning of their next visit.

### **3.1.2 Visit 3 (Day 28 $\pm 2$ )**

Subjects will return to the clinic on Day 28 ( $\pm 2$ ). Daily diaries will be collected and reviewed. All remaining study product and packaging will be returned. A new supply of study product will be dispensed.

At this visit, the following visit procedures will occur:

- Review changes in medication and adverse events
- Collection of vital signs (seated resting blood pressure and heart rate)

- Measurement of weight and calculation of BMI
- Calculation of investigational product compliance
- Taste and tolerability questionnaire
- Blood sample: Serum phospholipid fatty acids
- Administration of IP
- Daily treatment diary will be dispensed

Subjects will be given their daily dose of the study product in the clinic with a snack.

Paper diaries will be provided to subjects for recording study product use, change in concomitant therapies, and any side effects/changes in current conditions.

Subjects will be reminded not to change dietary habits and activity/training level during the study and to avoid consuming alcohol for at least 24 hours prior to the next study visit.

The next visit will be scheduled for Day 84. In the event that this is not possible due to subject scheduling issues, a visit window of  $\pm 2$  days may be applied.

#### **3.1.3 Visit 4 (Day 84 $\pm$ 2)**

Subjects will return to the clinic on Day 84 ( $\pm 2$ ). Daily diaries will be collected and reviewed. All remaining study product and packaging will be returned. A new supply of study product will be dispensed.

At this visit, the following visit procedures will occur:

- Review changes in medication and adverse events
- Collection of vital signs (seated resting blood pressure and heart rate)
- Measurement of weight and calculation of BMI
- Calculation of investigational product compliance
- Taste and tolerability questionnaire
- Blood sample: RBC fatty acid profile
- Administration of IP
- Daily treatment diary will be dispensed

Subjects will be given their daily dose of the study product in the clinic with a snack.

Paper diaries will be provided to subjects for recording study product use, change in concomitant therapies, and any side effects/changes in current conditions.

Subjects will be reminded not to change dietary habits and activity/training level during the study and to avoid consuming alcohol for at least 24 hours prior to the next study visit.

The next visit will be scheduled for Day 112. In the event that this is not possible due to subject scheduling issues, a visit window of  $\pm 2$  days may be applied. Subjects will be asked not to take their study product on the morning of their next visit.

#### **3.1.4 Visit 5 (Day 112 $\pm$ 2)**

Subjects will return to the clinic on Day 112 ( $\pm 2$ ). Daily diaries will be collected and reviewed. All remaining study product and packaging will be returned. A new supply of study product will be dispensed.

At this visit, the following visit procedures will occur:

- Review changes in medication and adverse events
- Collection of vital signs (seated resting blood pressure and heart rate)
- Measurement of weight and calculation of BMI
- Calculation of investigational product compliance
- Taste and tolerability questionnaire
- Blood sample: RBC fatty acid profile
- Administration of IP
- Daily treatment diary will be dispensed

Subjects will be given their daily dose of the study product in the clinic with a snack.

Paper diaries will be provided to subjects for recording study product use, change in concomitant therapies, and any side effects/changes in current conditions.

Subjects will be reminded not to change dietary habits and activity/training level during the study. Subjects will be asked to fast for at least 12 hours (nothing to eat or drink except water) prior to the visit and avoid consuming alcohol for at least 24 hours prior to visit 1.

The next visit will be scheduled for Day 168. In the event that this is not possible due to subject scheduling issues, a visit window of  $\pm 2$  days may be applied. Subjects will be asked not to take their study product on the morning of their next visit.

### **3.1.5 Visit 6 (Day 168 $\pm 2$ )**

Subjects will return to the clinic on Day 168 ( $\pm 2$ ) for a final study visit. Daily diaries will be collected and reviewed. All remaining study product and packaging will be returned.

At this visit, the following visit procedures will occur:

- Review changes in medication and adverse events
- Collection of vital signs (seated resting blood pressure and heart rate)
- Measurement of weight and calculation of BMI
- Calculation of investigational product compliance
- Taste and tolerability questionnaire
- Urine pregnancy test (for women of childbearing potential only).
- Blood sample: CBC, AST, ALT, BUN, creatinine, eGFR, electrolytes (Na, K, Cl), and lipid profile (total cholesterol, LDL-C, HDL-C and triglycerides), RBC fatty acid profile

### **3.1.6 Unscheduled Visits**

Any study participant who contacts the CRO about possible adverse events that are more than minor and/or that persist will be asked to visit the research centre for an assessment as appropriate.

### **3.1.7 Early Termination/Discontinuation Visit**

Participants may withdraw voluntarily from participation in the study at any time. Subjects will be encouraged to visit the clinic for an early termination visit. At this visit, subjects will be encouraged to return study product and diaries, have blood pressure, heart rate and weight measured and provide a blood sample for analysis of safety parameters (hematology and clinical chemistry).

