### **2.2 Additional Objectives**

An additional objective of this clinical study is to assess the tolerability of the fish oil supplements over 6 months of supplementation.

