| Randomization                                                                                                                                                  |            |                     | X       |            |            |             |             |
| Blood Sample: Serum Phospholipid Fatty Acids                                                                                                                   |            |                     | X       | X          |            |             |             |
| Blood Sample: Total Red Blood Cell Fatty Acid Profile                                                                                                          |            |                     | X       |            | X          | X           | X           |
| Investigational Product Dispensed                                                                                                                              |            |                     | X       | X          | X          | X           |             |
| Investigational Product Returned                                                                                                                               |            |                     |         | X          | X          | X           | X           |
| Treatment Diary Dispensed                                                                                                                                      |            |                     | X       | X          | X          | X           |             |
| Treatment Diary Returned                                                                                                                                       |            |                     |         | X          | X          | X           | X           |
| Taste and Tolerability Questionnaire                                                                                                                           |            |                     |         | X          | X          | X           | X           |
| Review Adverse Events                                                                                                                                          |            |                     |         | X          | X          | X           | X           |

 Height will be measured at visit 1 only

 Urine pregnancy test is for women of childbearing potential only

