#### 4.4 Withdrawal Criteria

A participant may end his/her participation in a study at any time without consequence. If a participant withdraws from the study, the Investigator will make a reasonable effort to determine the reason for withdrawal from the study and record any adverse events experienced by the subject.

**Personal reasons (participant initiated):** As stated in the ICF, participants will be informed that their participation in the study is optional, and they can withdraw from the study at any time, without consequence or prejudice.

**Clinical judgment of investigator/physician:** A participant could also be withdrawn from the study if, in the opinion of the treating physician, it is not in the participant's best interest to continue (e.g. pregnancy, adverse events, need for prohibited medication, illness). In the event that a female participant becomes pregnant during the study, she will be withdrawn from the study immediately, and the pregnancy followed to resolution. Further, spontaneous abortion or any congenital anomaly/birth defect, in the case of a live birth, must be reported as an SAE to the REB and Health Canada within 15 days of becoming aware of the event. All serious adverse events will result in withdrawal from the trial.

**Protocol violation:** Participants who fail to comply with the protocol may be removed at the discretion of the investigator.

Subjects Participants who wish to withdraw from the study will be asked for their reason(s). Reason(s) for participant withdrawal will be recorded on the CRF for all participants who sign the informed consent form.

Reasons for withdrawal will be documented as one of the following:

- W.1 Participant requests withdrawal from the study
- W.2 Participant withdraws consent
- W.3 AE makes the continuation of the participant impossible or inadvisable
- W.4 Participant was incorrectly included in the study (discovered after enrollment not to have met the protocol entrance criteria)
- W.5 Participant refuses to comply with required study procedures
- W.6 Participant has confirmed pregnancy

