## **8.2 Sample Size**

For this study, twenty four (24) subjects per group are expected to complete the study. With an expected attrition rate of 20%, thirty (30) subjects per group are required for this study. A formal sample size was not done for this investigative study.

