## **8.6 Handling of Missing or Spurious Data**

In the case of outliers or spurious data, that is, data that is not plausible, a rule of plus or minus 3 standard deviations of the mean will be applied to determine if the value should be excluded from analysis. All missing data or data excluded from analysis will be detailed in the final report. Missing values for primary and secondary endpoints at visits 3, 4, 5 or 6 will be imputed with the more recent previously-available value (LOCF, or “last-observation-carried-forward” imputation). No imputation will be performed for any missing daily diary variables, taste and tolerability questionnaire values or missing values of parameters of safety.

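### The Taste and Tolerability Questionnaire is not given at the early termination visit, so its later-visit results describe only participants who stayed in the study

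*Protocol*

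**What the plan says.** Protocol Section 2.2 states an additional objective, to "assess the tolerability of the fish oil supplements over 6 months of supplementation". It names no instrument.

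Table 1 lists the "Taste and Tolerability Questionnaire" at Visits 3, 4, 5 and 6 (Days 28, 84, 112 and 168), and the visit narratives agree. Table 1 has no early termination column.

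Section 3.1.7 sets out what happens when someone leaves early. Beyond returning product and diaries, participants are encouraged to "have blood pressure, heart rate and weight measured and provide a blood sample for analysis of safety parameters (hematology and clinical chemistry". The questionnaire is not mentioned.

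On missing data, Section 8.6 says: "No imputation will be performed for any missing daily diary variables, taste and tolerability questionnaire values or missing values of parameters of safety".

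On the expected loss, Section 8.2 says: "With an expected attrition rate of 20%, thirty (30) subjects per group are required for this study".

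**The concern.** Whether a questionnaire exists at a given visit depends on whether the participant is still in the study. That may in turn depend on what the form measures, namely how well the participant gets on with five capsules a day. Someone who stops in the first month because of reflux or aftertaste never fills it in. Someone who stops between two visits is represented only by the form from the earlier visit, completed before the decision to stop.

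Questionnaire results at Days 84, 112 and 168 are then conditional on having stayed. If intolerance is a material cause of withdrawal, they will tend to show better tolerability over 6 months than the randomized participants experienced.

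This is not something to leave to an analysis plan. Such a plan can decide how to summarise the forms that exist, but it cannot recover one that was never given.

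**Working it through.** **The protocol's own figure.** Section 8.2 expects 24 completers per group and 20% attrition. 24 / (1 − 0.20) = 30 per group, which matches. The expected loss is 30 − 24 = 6 per group, or 12 of 60.

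**Who lacks what.**
- Leaving before Visit 3 (Day 28): no questionnaire at all.
- Leaving later: the forms from visits attended, but none from the time of stopping. The longest gaps between forms, on nominal days, are 84 − 28 = 56 and 168 − 112 = 56 days, so the last form can be up to about eight weeks old.
- The protocol does not say how the 6 leavers per arm split between these two cases.

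**How far completer-only results could be off.** The protocol gives no intolerance rate, no split of attrition by reason, and no yes/no definition of poor tolerability. What follows is an illustration on assumed inputs. Suppose 2 of the 24 completers in an arm report poor tolerability, and k of the 6 leavers were intolerant. The completer-only rate is 2/24 = 8.3%. The rate with leavers counted is (2 + k)/30.

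| k (assumed) | All 30 | Completer-only minus all |
|---|---|---|
| 0 | 2/30 = 6.7% | +1.7 points |
| 2 | 4/30 = 13.3% | −5.0 points |
| 3 | 5/30 = 16.7% | −8.3 points |
| 6 | 8/30 = 26.7% | −18.3 points |

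Under these assumptions the completer-only figure lies between 1.7 points too high and 18.3 points too low. The direction is favourable only if a fair share of leavers were intolerant; with k = 0 it is slightly unfavourable.

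**What the other sources record for leavers.**
- Adverse events (Section 7.1.1) are volunteered or observed, with one general question at each visit. That is not the same set of items that stayers answer, and dislike of the taste need not be an adverse event.
- Withdrawal reasons (Section 4.4) include W.3 for an adverse event but no code for taste or tolerability. A participant who leaves over taste could be coded W.1, a participant request.
- Diaries record side effects, but their return at early termination is only encouraged, and missing diary variables are not imputed.

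These sources show that a person left and often why. They do not supply the questionnaire items at the time of stopping.

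**The case against.** The strongest reply is that the protocol follows leavers by several routes that need no scheduled visit. Section 4.4 says "the Investigator will make a reasonable effort to determine the reason for withdrawal from the study and record any adverse events experienced by the subject". Section 3.1.6 brings in participants with persistent or more than minor events. The safety population in Section 8.3.2 requires one dose and no later visit. Section 8.5 summarises adverse events by treatment group and provides for Fisher's exact or chi-square comparisons. Section 8.7 lists every premature discontinuation with its reason. A participant who stops on Day 10 with reflux should therefore appear as a graded adverse event in that arm's rate and in the listing.

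This stands, and it rules out three stronger readings that a reader might infer:

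- That tolerability is measured only in those who reach scheduled visits, or that intolerant leavers vanish from the results. The routes above keep them in the record, and no section makes the questionnaire the sole instrument for the objective.
- That the plan will distort a comparison of tolerability between the products. Unequal loss could do that to the questionnaire, but the protocol states no between-product test of it. The comparison it does state, of adverse events in all dosed participants, does not require anyone to stay in.
- That leaving questionnaire values unimputed is itself an error. It is a reasonable choice; the gap lies in not collecting the form.

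It is also fair that anyone who attended Visit 3 will normally have contributed at least one form, and that the choice of summary tables may properly sit in an analysis plan that is not shown. The reply does not explain why an existing form should be left out of an existing visit when the alternative sources do not ask the same questions.

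**Conclusion.** The point holds as a gap in data collection. The questionnaire is missing at discontinuation, so its results at later visits are conditional on remaining in the study and are probably too favourable if intolerance drives withdrawal. At the planned attrition this concerns up to 6 of 30 per arm.

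The size of the bias is unknown. The table above shows only what assumed splits would produce, and it should not be read as an estimate. The direction rests on the assumption that a meaningful share of leavers stop because of taste or intolerance, which the protocol neither states nor excludes.

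Severity is low. Tolerability is an additional objective, the questionnaire is not among the endpoints in Sections 6.1 and 6.2, and neither the primary nor the secondary endpoints are affected.

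**What to change.** - Add the Taste and Tolerability Questionnaire to the early termination visit in Section 3.1.7, and add that visit to Table 1. Where the participant does not attend, complete the form by telephone. Its answers should refer to the time on product.
- Report the last on-product questionnaire for all dosed participants, beside discontinuations by arm and by every recorded reason. W.3 alone would miss those who leave over taste and are coded W.1.

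The cost is one short existing form, at an existing visit or in a call, for about 12 people, plus one extra table. Sample size, dosing and the primary analysis do not change. The form will be recovered only from leavers who attend or can be reached. Reported tolerability may look slightly worse.

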### 3.2 Diagnostic Tests

Subjects will be asked to fast for at least 12 hours (nothing to eat or drink except water) prior to the screening (Visit 1) and end of study visit (Visit 6). At these visits, blood samples will be collected by venipuncture for analysis of CBC, AST, ALT, BUN, Creatinine, eGFR, glucose, electrolytes (Na, K, Cl) and lipid profile (total cholesterol, LDL-C, HDL-C and triglycerides. Additionally, blood samples (no requirement for fasting) will be collected by venipuncture for analysis of total RBC fatty acids at visits 2, 4, 5 and 6, and serum phospholipids at visits 2 and 3.

The volume of blood to be collected is approximately 14mL at visit 1, 10mL at Visits 2 and 3, 5mL at visits 4 and 5 and 19mL at visit 6. The total amount of blood collected over the 6 month study period will be approximately 63mL.

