### 3.4 Stopping Rules/Discontinuation

The investigator may withdraw any participant from this research if circumstances arise that warrant doing so. If a participant is withdrawn from the study for any reason, they will be asked to complete an early termination visit.

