### **6.1 Primary Endpoints**

The primary endpoints are red blood cell EPA and DHA after 6 months (24 weeks) of supplementation and serum phospholipid fatty acid analysis after 1 month of supplementation.

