## **7.4 Hematology and Clinical Chemistry**

Fasting (12 hours) blood samples will be collected at screening (Visit 1) and week 12 (Visit 6) at the end of the treatment period. Samples will be analyzed for complete blood count (CBC) with differential (hemoglobin, hematocrit, white blood cell count with differential, red blood cell count and platelet count), BUN, creatinine, eGFR, AST, ALT, and electrolytes (Na, K, Cl).

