## **8.3 Analytical Populations**

### **8.3.1 Intent-To-Treat Population**

Any subject known to start treatment (known to have taken  $\geq 1$  dose of study product) and completing at least one post-baseline visit will be included in the analysis of efficacy (intention-to-treat population).

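### The early termination visit takes no red cell fatty acid sample, so a participant who leaves between Visits 3 and 4 enters the 24-week primary analysis with the Day 0 value

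*Protocol*

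**What the plan says.** All of the relevant rules are in the protocol.

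- **Early termination visit (3.1.7).** Leavers are encouraged to attend and to "provide a blood sample for analysis of safety parameters (hematology and clinical chemistry"). The panel in 7.4 is a blood count with differential plus "BUN, creatinine, eGFR, AST, ALT, and electrolytes (Na, K, Cl"); it contains no fatty acids.
- **Who is asked (3.4 Stopping Rules/Discontinuation).** "If a participant is withdrawn from the study for any reason, they will be asked to complete an early termination visit".
- **Fatty acid sampling (3.2 Diagnostic Tests; Table 1).** Blood is drawn for "analysis of total RBC fatty acids at visits 2, 4, 5 and 6, and serum phospholipids at visits 2 and 3". Visit 3 therefore has no red cell sample.
- **Primary endpoint (6.1).** "The primary endpoints are red blood cell EPA and DHA after 6 months (24 weeks) of supplementation", together with serum phospholipid fatty acids at 1 month.
- **Efficacy population (8.3.1).** A participant who has taken a dose and is "completing at least one post-baseline visit will be included in the analysis of efficacy". No post-baseline fatty acid value is required.
- **Missing data (8.6).** "Missing values for primary and secondary endpoints at visits 3, 4, 5 or 6 will be imputed with the more recent previously-available value". Baseline is not excluded as a source.
- **Attrition (8.2 Sample Size).** "With an expected attrition rate of 20%, thirty (30) subjects per group are required for this study".

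**The concern.** Each rule is understandable alone, but together they leave a gap. The protocol expects a fifth of participants to leave, invites every one of them back and draws blood when they come, yet omits the sample that a primary endpoint needs. For a participant who leaves after Visit 3 but before Visit 4, the only red cell value on file was taken before the first capsule. The carry-forward rule then reports that value as the 24-week result.

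Up to about 12 weeks of treatment would then be scored as no response. If this happens equally in both arms, the observed difference shrinks. If it happens more in one arm, the product comparison itself moves. No later choice of analysis can recover a sample that was not drawn, so the gap has to be closed at the data collection stage.

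**Working it through.** **1. The plan's own figure.** 24 expected completers and 20% attrition give 24 / (1 − 0.20) = 30 per arm, as stated in 8.2. Expected leavers are 30 − 24 = 6 per arm, or 12 in all.

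**2. Which red cell value each leaver carries.** The protocol does not give the timing of leaving. As an assumption, spread the 6 leavers evenly over 168 days, so that the expected number in a window is 6 × (days in window) / 168.

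| Leaves between | Expected per arm | Last red cell value | Age of that value at Day 168 |
|---|---|---|---|
| Day 0 and Day 28 | 6 × 28/168 = 1 | Day 0 | 168 days, if analysed at all (see step 4) |
| Day 28 and Day 84 | 6 × 56/168 = 2 | Day 0 | 168 days |
| Day 84 and Day 112 | 6 × 28/168 = 1 | Day 84 | 84 days |
| Day 112 and Day 168 | 6 × 56/168 = 2 | Day 112 | 56 days |

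**3. Effect on the mean difference.** Let f be the share of each arm whose 24-week value is the carried Day 0 value. The analysis of covariance in 8.4 adjusts for baseline, so a carried baseline value counts as zero change. With mean responses A and B in the two arms and the same f in both, the expected difference is (1 − f)A − (1 − f)B = (1 − f)(A − B). The share kept is 1 − f, and the ratio of the two responses is unchanged. This treats Day 84 and Day 112 values as standing in fully for Day 168, so it isolates the Day 0 problem.

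- No one leaves between Visits 3 and 4: f = 0, 100% kept.
- Uniform leaving, with the one leaver before Visit 3 not analysed: f = 2/29, and 27/29 = 93% kept.
- All 6 leave between Visits 3 and 4: f = 6/30, and 24/30 = 80% kept.

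**4. An open point in 8.3.1.** It is not settled whether a termination visit counts as a post-baseline visit. If it does, the leaver before Visit 3 is also analysed with a Day 0 value. Under uniform leaving f becomes 3/30, and 90% is kept. That participant's Day 28 serum phospholipid endpoint would also be filled from Day 0.

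**5. Unequal leaving, for illustration only.** The labelled daily EPA plus DHA is 5 × (325 + 225) = 2750 mg for Ultimate Omega and 5 × (300 + 200) = 2500 mg for Meg-3, a ratio of 1.10. Suppose response is proportional to labelled dose (an assumption) and call the comparator response R, so that the true contrast is 0.10R.

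- Two of 29 carried at Day 0 in the Ultimate Omega arm only: 1.10R × 27/29 − R = 0.024R.
- Two of 29 carried at Day 0 in the comparator arm only: 1.10R − R × 27/29 = 0.169R.

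These steps concern the mean difference. They are not power figures: the protocol gives no effect size or standard deviation, and 8.2 says no formal calculation was made.

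**The case against.** The case on the other side is that the effect is small and partly speculative. Much of this stands.

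- A reader might infer that leavers contribute no fatty acid data at all. They do. Everyone who attends Visit 3 is due to give the serum sample for the other primary endpoint, and anyone leaving after Visit 4 has an on-treatment red cell value. Under uniform leaving that covers 3 of the 6 leavers per arm.
- A reader might set the 7% dilution (2/29) against the 10% dose contrast and conclude that the comparison is nearly lost. The documents do not support that. Equal dilution turns a 10% contrast into about 9.3% (10% × 27/29) and leaves the ratio between products unchanged. The large shifts in step 5 need an imbalance, and the protocol predicts none.
- Attendance is only encouraged, and some who withdraw consent may give no blood, so the extra tube will not reach every leaver.
- A sample taken on leaving is not a 24-week sample. For someone who has stopped the product, it is not clearly the value they would have had at Day 168.

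The last point limits the remedy but does not remove the concern. The stated endpoint is red cell EPA and DHA after 24 weeks of supplementation. Where the plan must carry a value forward, one taken during or just after supplementation bears on that endpoint, and a pre-treatment value does not. Nor can the point be left to a statistical analysis plan, because the protocol fixes both the sampling limit and the carry-forward rule.

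**Conclusion.** The point holds for a defined group: participants who attend Visit 3, leave before Visit 4, and are then scored at 24 weeks with a Day 0 value that is 168 days old at the endpoint.

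The number affected depends on when people leave, which the protocol does not say. It is about 2 of 29 per arm under uniform leaving, and between 0 and 6 of 30 overall. The share of the true difference kept is accordingly about 93%, within a range of 100% to 80%.

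The documents establish possible dilution. They do not establish bias between products, which arises only if early leaving differs by arm. The change is worth making because it is cheap and protects a primary endpoint. The expected distortion is modest.

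**What to change.** Add one red cell fatty acid tube to the early termination visit in 3.1.7, and add that visit as a column in Table 1. Record the actual sampling day, and state in 8.6 that this sample serves as the last available value when later red cell values are missing.

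**What it achieves.** With full attendance, the expected Day 0 carry-forwards under uniform leaving fall from about 2 per arm to 0. The 24-week value is still missing for leavers, so the carry-forward problem is reduced and not removed. Modelling the sample at its own day would be a separate change to the analysis and is not needed for this fix.

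**What it costs.** The tube takes about 5 mL, the volume that 3.2 Diagnostic Tests gives for Visits 4 and 5, where only red cell fatty acids are drawn. It comes from a venipuncture already planned, and that section requires no fasting for fatty acid samples. At the planned attrition this is at most about 12 assays, plus a short amendment and consent wording.

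**One linked decision.** State in 8.3.1 whether the termination visit counts as a post-baseline visit. A serum phospholipid tube for participants leaving before Visit 3 is useful only if it does.
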